### Standard of Care Study Procedures

All families will receive all routine pediatric care, and families enrolled in the Control group will receive standard HealthySteps.

### Care Provider Study Procedures

Directly after consent, at the time of initial implementation of the HealthySteps+PlayReadVIP program—that is, enrollment and baseline assessment of first participants—providers will be asked to complete the baseline survey. Then, at 6 and 18 months following consent and initial implementation of HealthySteps+PlayReadVIP, enrolled care providers will be asked to complete online surveys related to implementation outcomes, including appropriateness of the intervention, and acceptability for both parent participants and providers. These assessments are equivalent in timing to the first 12 and 24 month parent-child assessments. In addition, prior to initial implementation and at the two following assessment points, providers will be asked to complete surveys related to attitudes towards evidence-based programs, clinic climate, and their feelings of competency and understanding of the HealthySteps+PlayReadVIP program. Baseline assessments prior to any implementation of the HealthySteps+PlayReadVIP program are expected to take approximately 15 minutes, and assessments at 6 and 18 months following initial implementation will take up to 30 minutes. Providers will be able to access and complete the surveys at a time convenient to them, and will be encouraged to complete surveys outside of their normal work hours in order to reduce bias and maintain confidentiality.

In addition to these surveys, qualitative interviews will be used to gain an in depth understanding of barriers and perceptions to implementation, building on the information from the quantitative surveys.

## Study Schedule

### Screening

**Screening Visit (Day -3 to -1)**

- Review medical history to determine eligibility based on inclusion/exclusion criteria.
- Confirm eligibility in person with potential participants based on inclusion/ exclusion criteria, including primary language (i.e., administer the language screener when English or Spanish is not the primary language), ability to provide consent (i.e., test participant’s comprehension of study procedures and components), and viable contact methods (phone or email) for future participation in the study.

### Enrollment/Baseline

**Enrollment/Baseline Visit (Visit 1, Day 0)**

- Obtain informed consent of potential participant verified by signature on study informed consent form.
- Verify inclusion/exclusion criteria.
- Obtain demographic information, baseline information regarding parent health, mental health, the home environment, social determinants of health, and children’s development.

### Intermediate Visits

**Visit 2 (Day 180 +/- 90)**

- Record adverse events as reported by participant or observed by investigator.
- Administer questionnaires/surveys of parent well-being, parenting, and child development, and conduct parent-child observations
- Administer questionnaires to parents and care providers regarding program acceptability, appropriateness, and reach.
- Record participant’s engagement to intervention program and program fidelity and reach.

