# Schematic of Study Design

Approximately 1000 **individuals** -500 parent-infant dyad

dyad)

Randomize

Parent surveys, demographic information, and baseline measures of parenting assets, vulnerabilities

Families receive intervention (HS+PlayReadVIP or standard HS)

Parenting, ERH, and ECD outcomes, as well as intervention acceptability assessed through surveys, observations, and direct assessments

Parenting, ERH, and ECD outcomes, as well as intervention acceptability assessed through surveys, observations, and direct assessments

Qualitative interviews focusing on family needs, resources, and context

Baseline

0–24 months

Child age 12m; 6+ months post-enrollment

Child age 24m; 18 months post-enrollment

End of study (child age 24m)

Families with infants ≤6M, randomized into HS+PlayReadVIP or standard HS groups

Approximately **25** individual care providers

Acceptability & appropriateness of intervention; clinic climate & processes

Qualitative interviews of implementation outcomes

Acceptability & appropriateness of intervention; clinic climate & processes

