# Study Design and Endpoints

## Description of Study Design

**Overall Study Design:**

Randomized Controlled Trial (RCT): 500 families will be enrolled between birth and 6 months of child age and randomized to 1) HealthySteps+PlayReadVIP or 2) standard HealthySteps; with intervention delivery and assessments of parenting assets/vulnerabilities, parenting practices/relationships and child development from enrollment to child age 2 years.

**1. Setting:** Enrollment, randomization, and intervention delivery will take place at the NYU Langone Sunset Park Family Health Centers (SPFHC) pediatric clinic. The SPFHC is a federally-qualified health center, consisting of co-located prenatal and pediatric clinics with 10 pediatric providers (nine pediatricians; one nurse practitioner) and designated space for intervention delivery and assessments. It is across the street from NYU Langone Hospital–Brooklyn (NYULHB). NYULHB has ~4,000 births/year with 25-30% pediatric follow-up at the SPFHC. In total from July 2021-June 2022, the SPFHC served 3,503 children ages 0-3 (84% Hispanic, 10% Black/African-American, 3% Asian). In a recent needs assessment, 54% of families surveyed (*n*=401) reported multiple needs related to ACEs and parenting.^137^ 96% of these families had insurance coverage through Medicaid or CHIP.

**2. Sampling:** A consecutive sample of 620 parent-infant dyads presenting to HCC pediatric clinic will be assessed for eligibility, with ~500 families enrolled (expected ~5% not meeting eligibility and refusal rate ~10-15%). Feasibility is based on the current rate of target-age dyads (~1000 newborns/year presenting for care at SPFHC), and will build upon processes developed for ongoing intervention studies at SPFHC and elsewhere. In addition, program and other care providers will be approached through passive recruitment methods to complete surveys and interviews related to program implementation.

**3. Eligibility criteria:** Parent/infant dyads enrolled between birth and 6 months. Specific inclusion/exclusion criteria are given in Section 4.

**4. Intervention:** HealthySteps+PlayReadVIP Additional details given in Section 6.

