## Inclusion Criteria for parent-child dyads

In order to be eligible to participate in this study as a parent/child dyad, including one parent and one child, the dyad must meet all of the following criteria:

1. Parent is a biological parent or legal guardian and at least 18 years of age
2. Infants must be ≤6 months old at the time of enrollment.
3. Parents/guardians must speak either English or Spanish to ensure they can fully engage with the intervention and assessments.
4. Families must be identified as Tier 3 HealthySteps participants, indicating higher levels of need based on clinic screening for factors such as:Adverse Childhood Experiences (ACEs) and parenting challenges or vulnerabilities.
5. Parent is able to willing to provide consent for their own and their child’s participation.

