## Duration of Study Participation

Duration of study participation (screening, enrollment, randomization, intervention delivery, and follow-up) for parent-child dyads is approximately 2 years – from infant birth through age 2 follow up, which may take place prior to the child’s 3^RD^ birthday. Participation for care providers is approximately 1 year, with surveys and qualitative interviews taking place to coincide with age 12m and 24m parent-child assessments.

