**Assessment Procedures**

Assessments will be conducted at 12M and 24M (critical transition points for both parenting and child development) by highly trained, bilingual research staff, masked to intervention condition, to reduce bias. Assessments will last ~1 hour, in line with prior studies of parents of young children. Assessments will include surveys/questionnaires, observations of parents and children, and direct child assessments.

Outcomes to be assessed via questionnaire include:

|  | | | | | |
| --- | --- | --- | --- | --- | --- |
| **Level** | **Construct** | **Instrument** | **Base-line** | **12M** | **24M** |
| Effectiveness Outcomes | | | | | |
| Parent | **Parent-Child Relationship Quality** | Adult-Child Relationship Scale (*α*=.69-.84)^142^ |  | x | x |
|  | **Responsivity/Cognitive Stimulation** | StimQ Reading, Teaching/Play, Verbal Responsivity (*α*=.88)^143^ |  | x | x |
|  | Stress/Mental Health | Edinburgh Depression Scale (*α*=.77-.86)^144^, Perceived Stress Scale ( *α*=.75-.91);^145^ | x | x | x |
|  | Self-Efficacy | Parenting Self-Agency Measure (*α*=.68-.7)^146^ | x | x | x |
|  | Social Support | General Life Satisfaction (*α*=.91),^147^ Dyadic Adjustment Scale (*α*=.7-.95)^148^ | x | x | x |
|  | Structure | limit-setting, proactive parenting, feeding/sleep/screentime routines,^149^ Socolar Discipline Survey (*α*=.56-.82)^150^ |  | x | x |
|  |  | HealthySteps Parent Feedback Survey^170^ |  | x | x |
|  |  | Parenting Daily Hassles^171^ |  | x | x |
| Child | **Social Competence** | Infant Behavior Questionnaire (*α*=.75-.78),^151^ Brief Infant Toddler Social-Emotional Assessment (*α*=.69-.8)^152^ |  | x |  |
|  |  | Child Behavior Checklist (α=.9-.94)^153^ |  |  | x |
|  | Language & Cognitive Development | Early Social Communication Scale (*α*=.61-.91),^154^  MacArthur-Bates Communicative Development Inventories (*α*=.86);^155^  Dual Language Learners English-Spanish Inventories^172^ |  | x | x |
| Implementation Outcomes (CFIR, RE-AIM, CIHS) | | | | | |
| EBPI Provider (care-team member) | Acceptability | Acceptability of Intervention Measure (AIM; *α*=.89)^158^ |  | x | x |
|  | Appropriateness | Intervention Appropriateness Measure (IAM; *α*=.87)^158^ |  | x | x |
|  | CFIR Domains | Evidence-based Practice Attitudes Scale-36 (*α*=.80),^159^ clinic culture, perceived complexity of intervention, external policies, competence | x | x | x |
|  | Acceptability | Parent satisfaction surveys^117^ |  | x | x |
|  | | | | | |

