### Final Study Visit

***Final Study Visit (Visit 3, Day 540 +/- 90)***

- Record adverse events as reported by participant or observed by investigator.
- Administer questionnaires/surveys of parent well-being, parenting, and child development, and conduct parent-child observations
- Administer questionnaires to parents and care providers regarding program acceptability, appropriateness, and reach.
- Record participant’s engagement to intervention program and program fidelity and reach.
- Conduct qualitative interviews regarding program implementation with parents and care providers.

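### Visits 2 and 3 are timed from enrolment, but the 12M and 24M assessments are defined by child age, so infants enrolled in roughly their first three months cannot be seen at those ages within the stated windows

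*Protocol*

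**What the plan says.** Section 7.3 (Study Schedule) sets the clock at enrolment: "Enrollment/Baseline Visit (Visit 1, Day 0"). The first follow-up is "Visit 2 (Day 180 +/- 90"), which is Day 90 to Day 270. The last is "Final Study Visit (Visit 3, Day 540 +/- 90"), which is Day 450 to Day 630.

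Entry is wide relative to these windows. Section 4.1 says "500 families will be enrolled between birth and 6 months of child age", and the inclusion criteria repeat the upper limit without a lower one: "Infants must be ≤6 months old at the time of enrollment".

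Elsewhere the same assessments are placed by the child's age:

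- The schematic labels the first follow-up as child age 12 months, at six or more months after enrolment, and the second as "Child age 24m; 18 months post-enrollment".
- The assessment procedures in Section 7.1.1 give a developmental reason for the timing: "Assessments will be conducted at 12M and 24M (critical transition points for both parenting and child development").
- The mediation plan in Section 9.1 uses 12M mediators and 24M child outcomes.
- The planned interim analysis (Section 9.4.4) expects families to have had 6 to 12 months of the programme by the 12-month assessment.
- Section 5.5 describes participation as running "from infant birth through age 2 follow up, which may take place prior to the child" turns three.

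**The concern.** Staff have two rules for when to see a family, and for infants enrolled early the two cannot both be met.

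If the schedule is followed, one nominal time point mixes very different ages. The measures are tied to age: the infant behaviour and brief social-emotional questionnaires are given at 12M only, the behaviour checklist at 24M only, and the picture vocabulary tests at the 2-year visit. Under Section 7.3 an infant enrolled at birth could be given the 24M battery at about 15 months.

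If child age is followed, the intended endpoint is obtained, but many early-enrolled families fall outside the written window. The protocol's deviation section treats any noncompliance with the protocol as a deviation to be addressed and reported.

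**Working it through.** **Inputs.** Enrolment age 0 to 6 months, taken as 0 to 183 days (Sections 4.1 and 5.1). Windows Day 90–270 and Day 450–630 (Section 7.3). Target ages 12 and 24 months, taken as 365 and 730 days (schematic, Section 7.1.1). One month is 30.44 days unless stated.

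**Reproducing the plan's days.** Visit day = (target age − enrolment age) × days per month. For enrolment at exactly 6 months with 30-day months:

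- (12 − 6) × 30 = 180
- (24 − 6) × 30 = 540

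These are the stated days. With calendar months they are 183 and 548. The schedule is therefore written for an infant enrolled at the upper age limit.

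**Days needed across the enrolment range.** For enrolment between 6 months and birth, reaching 12 months takes about Day 183 to 365, and reaching 24 months about Day 548 to 730. The windows close up to 365 − 270 = 95 days and 730 − 630 = 100 days too early.

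**Youngest enrolment age that works.** Target age minus last window day gives the same figures: day 95 of life (3.1 months) for 12M and day 100 (3.3 months) for 24M. With 30-day months both are 90 days, exactly 3.0 months.

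**Child age inside the windows (months).**

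| Enrolled at | Visit 2 | Visit 3 |
|---|---|---|
| birth | 3.0–8.9 | 14.8–20.7 |
| 1 month | 4.0–9.9 | 15.8–21.7 |
| 2 months | 5.0–10.9 | 16.8–22.7 |
| 3 months | 6.0–11.9 | 17.8–23.7 |
| 4 months | 7.0–12.9 | 18.8–24.7 |
| 6 months | 9.0–14.9 | 20.8–26.7 |

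Overall, Visit 2 spans 0 + 90 = 90 to 183 + 270 = 453 days (3.0–14.9 months). Visit 3 spans 0 + 450 = 450 to 183 + 630 = 813 days (14.8–26.7 months).

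**Cross-checks.** Twelve months of delivery before the 12-month assessment implies visits as late as about Day 365, beyond the Day 270 limit. The schematic's six or more months after enrolment does not fit a window opening at Day 90. An age-2 visit allowed up to the third birthday does not fit a window in which the oldest possible child is about 26.7 months.

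**Share of families.** The protocol gives no distribution of enrolment age. If it were uniform over 0–183 days (assumption), 95/183 = 52% could not be seen at 12M and 100/183 = 55% could not be seen at 24M in window. The share rises with newborn recruitment and falls with later enrolment.

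**Illustrative precision loss.** Assume enrolment age uniform over 6 months and visit timing uniform over the 180-day window (5.9 months). The SD of age at a visit is √(6²/12 + 5.9²/12) ≈ 2.4 months. If an outcome changes by 0.1 to 0.2 of its fixed-age SD per month (assumption), its SD grows by a factor of √(1 + 0.24²) ≈ 1.03 to √(1 + 0.49²) ≈ 1.11, so d = .30 becomes about .29 to .27. With 200 per arm, power (two-sided 5%, normal approximation) goes from about 85% to about 83–77% without age adjustment.

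**The case against.** The intended reading is fairly clear. The schematic, the assessment procedures, the mediation plan and the expected 6 to 12 months of delivery all point to child age, and Day 180/540 look like nominal days for a 6-month enrollee. That stands as an account of how the conflict arose, but it does not remove it: the windows are the operational rule, and they close too early.

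The protocol states no age tolerance around 12M and 24M, but it does not say the tolerance is zero. With ±1 month the cut-off falls to about 2.1 and 2.3 months of age, with ±2 months to about 1.1 and 1.3, and at ±3 months the conflict nearly disappears. This stands as a limit on size.

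Three stronger readings are tempting but not supported:

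- A reader might infer that the age-specific endpoint is lost whichever rule is followed. Following child age delivers it; the cost is then window deviations.
- A reader might infer bias between arms. Baseline precedes randomisation and both arms share the same windows, so enrolment age is balanced in expectation.
- A reader might infer that a newborn enrollee could have Visit 2 before any session. That rests only on the 4-month start in the section on administering the intervention. The schematic shows delivery over 0–24 months, so session start is a separate inconsistency.

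Nor does every outcome clearly depend on child age; nothing in the protocol shows that parent depression or relationship adjustment does. The statements of assessments at 12 months and 2 years in Sections 4.1 and 7.1 give no anchor. Reading them as time since enrolment would conflict with Day 180/540 even more.

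**Conclusion.** The contradiction is real, and no reading of the protocol reconciles it. The windows in Section 7.3 fit the stated child ages only for infants enrolled after about day 95 (12M) or day 100 (24M) of life, and they admit ages spanning about 12 months at each visit. These figures rest on the protocol's own dates and on no assumed age tolerance. The share affected is unknown: about half under uniform enrolment, more or less under other patterns.

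The consequence is an inconsistent age-specific endpoint with some loss of precision if the schedule is followed, or avoidable deviations if child age is followed. The power range above is only an illustration, because the protocol gives no rate of change with age. It should be settled before follow-up begins, since age at testing cannot be changed once data are collected.

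**What to change.** In the entries for Visit 2 and the final visit, anchor the parent-child assessments to child age 12M and 24M, each with one stated window. Reconcile Section 5.5 with the 24M window: say how an assessment after that window but before the third birthday is classed, and keep it as data rather than discard it. Cutting the allowance outright would add missing data to the 15–20% attrition already planned for.

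Do not simply delete Day 180 and Day 540. The same visit entries carry the care-provider questionnaires, which the care-provider procedures place 6 and 18 months after consent and initial implementation. List those separately on that schedule.

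Record exact child age at each assessment and use it for age adjustment or a sensitivity analysis of the age-dependent child and parenting outcomes. Age at assessment is observed after randomisation, so it need not be imposed on every model.

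The cost is protocol wording, changed visit windows in REDCap and a little extra analysis. No visits are added.

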### Final Study Visit

***Final Study Visit (Visit 3, Day 540 +/- 90)***

- Record adverse events as reported by participant or observed by investigator.
- Administer questionnaires/surveys of parent well-being, parenting, and child development, and conduct parent-child observations
- Administer questionnaires to parents and care providers regarding program acceptability, appropriateness, and reach.
- Record participant’s engagement to intervention program and program fidelity and reach.
- Conduct qualitative interviews regarding program implementation with parents and care providers.

# Assessment of Safety

## Specification of Safety Parameters

This is a study behavioral and social aspects of parent-child interactions, promoting healthy development and reducing disparities in pediatric care. Minimal risk to participants is expected. There are no specific Adverse Events (AE) or Serious Adverse Events (SAE) related to study participation of which we are aware that can be specified in advance of the study.

### Definition of Adverse Events (AE)

An ***adverse event*** (AE) is any symptom, sign, illness or experience that develops or worsens in severity during the course of the study. Intercurrent illnesses or injuries should be regarded as adverse events. Abnormal results of diagnostic procedures are considered to be adverse events if the abnormality:

- results in study withdrawal
- is associated with a serious adverse event
- is associated with clinical signs or symptoms
- leads to additional treatment or to further diagnostic tests
- is considered by the investigator to be of clinical significance

This is a minimal risk study; any potential risks are described earlier (in ‘Risks’ section above). There are no AEs related to study participation that can be defined or specified in advance of the study.

### Definition of Serious Adverse Events (SAE)

**Serious Adverse Event**

Adverse events are classified as serious or non-serious. A ***serious adverse event*** is any AE that is:

- fatal
- life-threatening
- requires or prolongs hospital stay
- results in persistent or significant disability or incapacity
- a congenital anomaly or birth defect
- an important medical event

Important medical events are those that may not be immediately life threatening, but are clearly of major clinical significance. They may jeopardize the subject, and may require intervention to prevent one of the other serious outcomes noted above. For example, drug overdose or abuse, a seizure that did not result in in-patient hospitalization, or intensive treatment of bronchospasm in an emergency department would typically be considered serious.

All adverse events that do not meet any of the criteria for serious should be regarded as ***non-serious adverse events***.

### Definition of Unanticipated Problems (UP)

**Unanticipated Problems Involving Risk to Subjects or Others**

Any incident, experience, or outcome that meets all of the following criteria:

- Unexpected in nature, severity, or frequency (i.e. not described in study-related documents such as the IRB-approved protocol or consent form, the investigators brochure, etc)
- Related or possibly related to participation in the research (i.e. possibly related means there is a reasonable possibility that the incident experience, or outcome may have been caused by the procedures involved in the research)
- Suggests that the research places subjects or others at greater risk of harm (including physical, psychological, economic, or social harm).

## Classification of an Adverse Event

### Severity of Event

For AEs not included in the protocol defined grading system, the following guidelines will be used to describe severity:

- **Mild** – Events require minimal or no treatment and do not interfere with the participant’s daily activities.
- **Moderate** – Events result in a low level of inconvenience or concern with the therapeutic measures. Moderate events may cause some interference with functioning.
- **Severe** – Events interrupt a participant’s usual daily activity and may require systemic drug therapy or other treatment. Severe events are usually potentially life-threatening or incapacitating.

